# Active management of the third stage of labour without controlled cord traction: a randomized non-inferiority controlled trial

**DOI:** 10.1186/1742-4755-6-2

**Published:** 2009-01-21

## Abstract

**Background:**

The third stage of labour refers to the period between birth of the baby and complete expulsion of the placenta. Some degree of blood loss occurs after the birth of the baby due to separation of the placenta. This period is a risky period because uterus may not contract well after birth and heavy blood loss can endanger the life of the mother. Active management of the third stage of labour (AMTSL) reduces the occurrence of severe postpartum haemorrhage by approximately 60–70%. Active management consists of several interventions packaged together and the relative contribution of each of the components is unknown. Controlled cord traction is one of those components that require training in manual skill for it to be performed appropriately. If it is possible to dispense with controlled cord traction without losing efficacy it would have major implications for effective management of the third stage of labour at peripheral levels of health care.

**Objective:**

The primary objective is to determine whether the simplified package of oxytocin 10 IU IM/IV is not less effective than the full AMTSL package.

**Methods:**

A hospital-based, multicentre, individually randomized controlled trial is proposed. The hypothesis tested will be a non-inferiority hypothesis. The aim will be to determine whether the simplified package without CCT, with the advantage of not requiring training to acquire the manual skill to perform this task, is not less effective than the full AMTSL package with regard to reducing blood loss in the third stage of labour.

The simplified package will include uterotonic (oxytocin 10 IU IM) injection after delivery of the baby and cord clamping and cutting at approximately 3 minutes after birth. The full package will include the uterotonic injection (oxytocin 10 IU IM), controlled cord traction following observation of uterine contraction and cord clamping and cutting at approximately 3 minutes after birth. The primary outcome measure is blood loss of 1000 ml or more at one hour and up to two hours for women who continue to bleed after one hour. The secondary outcomes are blood transfusion, the use of additional uterotonics and measure of severe morbidity and maternal death.

We aim to recruit 25,000 women delivering vaginally in health facilities in eight countries within a 12 month recruitment period.

**Management:**

Overall trial management will be from HRP/RHR in Geneva. There will be eight centres located in Argentina, Egypt, India, Kenya, Philippines, South Africa, Thailand and Uganda. There will be an online data entry system managed from HRP/RHR. The trial protocol was developed following a technical consultation with international organizations and leading researchers in the field.

**Expected outcomes:**

The main objective of this trial is to investigate whether a simplified package of third stage management can be recommended without increasing the risk of PPH. By avoiding the need for a manual procedure that requires training, the third stage management can be implemented in a more widespread and cost-effective way around the world even at the most peripheral levels of the health care system. This trial forms part of the programme of work to reduce maternal deaths due to postpartum haemorrhage within the RHR department in collaboration with other research groups and organizations active in the field.

**Trial Registration:**

ACTRN12608000434392

## Background

The third stage of labour refers to the period between birth of the baby and complete expulsion of the placenta. Some degree of blood loss occurs after the birth of the baby due to separation of the placenta. This period is a risky period because uterus may not contract well after birth and heavy blood loss can endanger the life of the mother.

The third stage of labour is managed differently around the world. Over the years two management packages, known as 'active management' and 'expectant management' emerged. The primary aim of active management is to reduce postpartum blood loss as a preventive intervention. In active management (AMTSL) a number of interventions are applied in combination while the expectant management represents a more hands-off style with those interventions used in AMTSL withheld. AMTSL has been defined in various ways and current international definition comprises three components: administration of an uterotonic soon after delivery of the baby; controlled cord traction; and uterine massage after delivery of the placenta [1]. Active management of the third stage of labour (AMTSL) reduces the occurrence of severe postpartum haemorrhage by approximately 60–70% [2].

In previous active versus expectant trials the cord was clamped as soon as possible usually within one minute. However, trials of cord clamping timing have shown beneficial effects on newborn haematological indices leading to the recommendation to clamp the cord at around 3 minutes although the effects on the mother are unknown [3].

The WHO PPH Prevention Guidelines published in 2007 recommended AMTSL defined as the use of oxytocin 10 IU IM/IV after birth, cord clamping at around 3 minutes when the uterus contracts and controlled cord traction. There were no recommendations related to the use of uterine massage in this guideline.

Unfortunately, the relative contribution of the components of AMTSL to the overall reduction in blood loss is not clearly known. Understanding the contribution of the components of AMTSL to the overall effect in reducing the incidence of haemorrhage could have major programmatic significance since some components require training while others require an efficient drug procurement and utilization system [4]. At the same time the probability of interaction between AMTSL components should be kept in mind.

These considerations led to a technical consultation of scientists working in the field of postpartum haemorrhage research in December 2007 to discuss work on a research project to evaluate the effects of different components of AMTSL. Such research is important and timely because some components such as the uterotonic and controlled cord traction may not be feasible in all settings and it is worthwhile evaluating a more simple package with fewer components.

### Systematic reviews of effects of AMTSL components

#### Uterotonic

The uterotonic component of AMTSL seems to be important for the reduction in blood loss after delivery [5]. Two trials compared oxytocin to nothing without other active management components practiced [6,7] and one trial compared oxytocin to nothing with other active management components practiced in both groups [8]. Oxytocin used at 5–10 IU seemed to reduce the risk of severe postpartum haemorrhage although the other components were not well described.

#### Controlled cord traction

Cord traction was introduced into obstetric practice by Brandt (1933) and Andrews (1940) by the so-called Brandt-Andrews maneuver. The aim is to facilitate the delivery of a placenta that is already separated. In 1962 the term *controlled cord traction *(CCT) was introduced which aims to facilitate the separation of the placenta once the uterus contracts [9]. In performing CCT placental separation is not waited and once the uterus contracts the CCT is initiated. The third stage is usually completed in less than 10 minutes when CCT is used.

There is concern by clinicians, based on teachings from their pre-service education that traction on the cord prior to placental separation may lead to maternal complications such as separation of the cord from the placenta and uterine inversion. There is not a large body of direct evidence for or against effects of controlled cord traction in isolation [10].

CCT requires training to acquire this manual skill. Evaluation of CCT component is important because if it does not add any beneficial effects it can be dropped from the AMTSL package with important programmatic implications.

#### Uterine massage

Uterine massage is used following delivery in various forms. Between delivery of the baby and the placenta a birth attendant will often put his/her hand over the uterus to ensure that there is no undiagnosed twin, to assess if the uterus is contracting and may rub the uterus to stimulate contraction. The Cochrane review on active versus passive management does not refer to the use of uterine massage as part of AMTSL whereas the FIGO/ICM statement on AMTSL does include uterine massage as part of AMTSL. Evidence that massage contributes to a reduction in blood loss would provide evidence to support the use of this intervention with simple instructions.

The National Institute for Health and Clinical Excellence of the United Kingdom published comprehensive guidelines on intrapartum management on 26 September 2007  and has made no reference to uterine massage.

A small pilot trial (n = 200) conducted in Assiut, Egypt, used 'sustained uterine massage' started after delivery applied every 10 minutes and continued for 60 minutes. The findings are promising, since women receiving massage had less blood loss > 500 ml and received less additional uterotonics than women not receiving uterine massage [11]. In the two surveys conducted by Prevention of Postpartum Hemorrhage Initiative (POPPHI) massage before placental delivery was practiced in about one third of all deliveries. In the same surveys massage after placental delivery was used in 80–90% of women although it was not possible to observe how long after delivery the massage was continued [12].

Williams Obstetrics states "massage is not employed but the fundus is frequently palpated to make certain that the organ does not become atonic and filled with blood from placental separation". In the United States and some other countries, palpating the uterus and massaging if "soft" for the first few hours after childbirth is considered standard of care [13]. In many countries however, no well-defined massage protocol exists. A systematic review to evaluate the effects of sustained uterine massage from the time of birth of the baby currently contains very little evidence to guide practice [14].

#### Other interventions

One intervention that has recently been included in AMTSL package is delayed cord clamping. There is evidence that delayed cord clamping increases newborn haematological indices in the short term and also has beneficial effects of reduced intraventricular haemorrhage when applied to preterm infants. However, there is almost no evidence on maternal effects especially whether it increases the blood loss.

Other third stage interventions include squeezing the uterus from the fundus to expel the placenta (Credé maneuver) [15], placental cord drainage, umbilical vein injection and variations in timing, dose, and route of above discussed components.

### Rationale for selecting the experimental intervention

An important aspect of AMTSL components is that one cannot assume that each component has no interaction with others. Such interactions could occur for single, double or triple components. The implication is that even if an intervention may not be (as) effective when individually applied it may have effect together with another component. For example, oxytocin and massage could act synergistically.

The relative importance of all of these uncertainties and the feasibility of evaluating the effects of one or more of the components were discussed in detail at the technical consultation referred above in December 2007. The evaluation of two components namely CCT and uterine massage after placental delivery was given priority. The feasibility of evaluating both interventions in one trial was discussed in detail. Different epidemiological designs such as three-arm and 2 × 2 factorial design were considered. Evaluating more than one component in a single trial posed particular difficulties. Such difficulties originated from the nature of the intervention(s) (manual procedures being difficult to mask) and the low incidence of the primary outcome measure. The implications of these two factors were resorting to cluster or cross-over cluster designs with added complexity and large sample sizes. At the end of the consultative process evaluation of a package that does not include controlled cord traction was regarded as the highest priority research question among all discussed. The main reason for this conclusion is that currently, the global scale up of AMTSL is limited to those settings where skilled birth attendants are available largely because controlled cord traction (CCT) requires clinical skills training. Considerable training investments are needed to enable health providers to do CCT correctly and safely.

The presence of a skilled birth attendant is essential in every childbirth. Birth attendants are required for not only basic care during the first and second stage of labour but also in the third stage when haemorrhage risk is greatest and also for the immediate care of the newborn. We aim to identify the relative effect of one component that requires manual skill training. In the most peripheral points of the health system the availability of health personnel with skills to implement the full AMTSL package may be more difficult to ensure in some settings. Therefore, evaluation of whether a simplified package without CCT is non-inferior to the full AMTSL package has both clinical and public health importance. The simplified package is also less intrusive for the mother.

If it were possible to demonstrate the non-inferiority of a simplified form of AMTSL, dispensing with CCT, it would greatly reduce programme costs associated with training, and enable the intervention to be used by lower level providers, especially in out-of-hospital settings.

We therefore put forward the hypothesis that a simplified package comprising oxytocin 10 IU IM/IV (with or without uterine massage) is as effective as the full AMTSL package.

### Objective

The primary objective is to determine whether the simplified package of oxytocin 10 IU IM/IV, without CCT, is not less effective than the full AMTSL package with regard to reducing blood loss ≥ 1000 ml in the third stage of labour. The hypothesis will be that of non-inferiority within a margin of 0.45 to 0.50%. If this hypothesis is demonstrated, the simplified package without CCT could be adopted, with the advantage of not requiring training to acquire the manual skill to perform this task.

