### Rationale for the non-inferiority hypothesis and for sample size estimation

The objective of this trial is to show 'non-inferiority' of the simplified package' compared to the full AMTSL package. As such, while superiority would be an added bonus it is not expected and is probably not plausible since the experimental intervention has fewer interventions.

In the conventional superiority trial, the aim is to determine whether one intervention is superior to another, for example, whether uterotonic is superior to nothing. By contrast, in a non-inferiority trial, the aim is to determine whether an alternative intervention with certain advantages is similar to a gold standard. The full AMTSL package represents the gold standard management strategy for reducing blood loss in the third stage of labour. In order to evaluate the effectiveness of a simplified package with fewer components that package has to be compared to the full package to see whether t is "non-inferior" to the gold standard [17].

Because proof of exact equality is impossible, a pre-stated margin of non-inferiority (Δ) for the difference in effectiveness has to be defined. The choice of the non-inferiority margin can be made using clinical assessment, which is to a certain extent arbitrary, and needs consensus among different stakeholders. A technique which has been proposed [17] to establish the non-inferiority margin is to look at the effect of the gold standard, in this case the full AMTSL, compared with placebo in historical (past) trials, in this case the expectant management. A reasonable criterion is to preserve 80% of the benefit of the full AMTSL package (considered as 100%) over expectant management (considered as 0%). Preserving a higher percentage (say 90%) will push the sample size calculations very high while a smaller percentage (say 50%) may not be considered acceptable.

Estimates of blood loss ≥ 1000 ml (severe PPH – sPPH) with active and passive management were taken from the literature. In addition, unpublished data from several ongoing WHO studies where postpartum blood loss is measured were obtained. Based on those data, a 1.5% risk of blood loss of 1000 ml with full active management was considered realistic and appropriate.

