The expectant management sPPH rate was more difficult to estimate because the data was only available from earlier published trials and blood loss estimation methods and the actual expectant management method differed between trials. Values between 3.0 to 4.0% are considered realistic and used for sample size estimations.

Table 1 includes different scenarios for the calculation of sample size, obtained by varying the sPPH rate with expectant management (3.0 to 4.0%) and varying the % retained effect (70% to 80%), assuming a fixed 1.5% sPPH rate for the full AMTSL package. These different scenarios result in different choices of the margin of non-inferiority **Δ**. The total sample size required for a non-inferiority test at the 2.5% level using a two-sided 95% confidence interval and a power of 80% is shown, as well as the power obtained for fixed sample sizes of 20,000 and 25,000.

**Table 1 T1:** Sample size scenarios

Blood loss ≥ 1000 ml with full amtsl	Blood loss ≥ 1000 ml with Expectant	Estimated impact of Full AMTSL	Proportion (of full AMTSL effect) retained by the simplified package	Δ (Difference to exclude to claim equivalence)	Total N for 80% Power	Power with total N = 20,000	Power with total N = 25,000
1.5	3.0	1.5	0.7	0.45	22,908	75%	83%

1.5	3.5	2.0	0.75	0.50	18,555	83%	90%

1.5	4.0	2.5	0.8	0.50	18,555	83%	90%

A trial of 22,908 women will have 80% power to show non-inferiority of the simplified package within 0.45% of the full AMTSL package sPPH rate (i.e. less than 1.95% sPPH rate), with a level of significance of 2.5% (Table 1, row 1). The estimates from the centres that have expressed interest in participating in the trial indicate that approximately 20,000–25,000 women can be recruited in a 12 months recruitment period. These centres have collaborated with WHO before and have experience in third stage trials.

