Randomization – Implementation	10	Who generated the allocation sequence, who enrolled participants, and who assigned participants to their groups.	4.4.2

Blinding (masking)	11	Whether or not participants, those administering the interventions, and those assessing the outcomes were blinded to group assignment. If done, how the success of blinding was evaluated.	4 (last sentence before 3.1)

Statistical methods	12	Statistical methods used to compare groups for primary outcome(s), *specifying whether a one or two-sided confidence interval approach was used*. Methods for additional analyses, such as subgroup analyses and adjusted analyses.	4.4.3 & 4.5

The actual management of third stage of labour will be recorded in all women to enable the analysis mentioned above.

Comparisons will be expressed as relative risks and risk differences with 95% confidence intervals. The analysis will be stratified by site, and if there is heterogeneity between the sites for any of the results possible causes of heterogeneity will be explored. In the presence of heterogeneity, the results will not be combined in a single summary estimate (or pooled estimate). In the absence of heterogeneity at the 5% level, the results will be combined.

The primary analysis will follow the following scheme for interpretation (Figure 1):[18] If the lower limit of the 95% confidence interval lies to the right of the non-inferiority margin (Δ) the experimental intervention will be declared "inferior" (situation H). Situations A-D indicate non-inferiority with respect to the pre-stated margin Δ. Situations E-G are inconclusive, although E and F are not likely to occur because the trial size guarantees sufficient power. If the results are inconclusive regarding the non-inferiority hypothesis and the whole 95% confidence interval lies to the right of zero (situation G), it will be concluded that the limited package was statistically significantly worse according to a superiority hypothesis.

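### The non-inferiority margin is stated as a range, 0.45 to 0.50 percentage points, while the decision rule needs a single pre-stated Δ

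*Protocol article*

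**What the plan says.** The sample size rationale in the protocol article accepts that "a pre-stated margin of non-inferiority (Δ) for the difference in effectiveness has to be defined". It proposes to derive Δ from the share of the full package's benefit over expectant management that must be kept: "A reasonable criterion is to preserve 80% of the benefit of the full AMTSL package".

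Table 1 then holds the full-package rate at 1.5% and varies the expectant rate (3.0, 3.5, 4.0%) and the retained share (70, 75, 80%). This gives Δ = 0.45, 0.50 and 0.50. The text comments: "These different scenarios result in different choices of the margin of non-inferiority". It selects none of them for the analysis. The sentence after the table uses row 1: "A trial of 22,908 women will have 80% power to show non-inferiority of the simplified package within 0.45" per cent.

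The Objective gives the formal hypothesis as a range: "The hypothesis will be that of non-inferiority within a margin of 0.45 to 0.50" per cent.

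The Analysis plan reads the primary result against one value: "Situations A-D indicate non-inferiority with respect to the pre-stated margin Δ". Situations E to G are inconclusive and H is inferior. No number is attached to Δ there.

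**The concern.** Where the upper 95% limit falls relative to Δ decides whether the trial supports dropping controlled cord traction. With a range in the hypothesis and one unnamed value in the decision rule, any upper limit between 0.45 and 0.50 can be read either way. The document does not say which reading applies.

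The choice also bears on how well sized the trial looks. The protocol expects 20,000 to 25,000 women. At 20,000, Table 1 gives 75% power for 0.45 and 83% for 0.50, so a recruitment shortfall would make the looser value more attractive. Women and caregivers know the allocation (Study design), so the value should be fixed before outcomes accumulate.

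**Working it through.** **Inputs.**
- Full-package risk 1.5%: "a 1.5% risk of blood loss of 1000 ml with full active management was considered realistic and appropriate".
- Expectant risk: "Values between 3.0 to 4.0% are considered realistic and used for sample size estimations".
- Two-sided 95% interval (one-sided 2.5%) and 80% power, from the sample size section.
- Recruitment target 25,000, from the Abstract.
- Assumption: 1:1 allocation, so 12,500 per arm. No ratio is printed.

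**1. The plan's own figures.** With a true difference of 0, n per arm = (1.960 + 0.8416)² × 2 × 0.015 × 0.985 / Δ².
- Δ = 0.0045: 11,453.6 per arm, rounded up to 11,454, total 22,908 (Table 1: 22,908).
- Δ = 0.0050: 9,277.4 per arm, rounded up to 9,278, total 18,556 (Table 1: 18,555, a rounding difference).

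Power = Φ(Δ/SE − 1.96), with SE = √(2 × 0.015 × 0.985 / n per arm). SE is 0.172 points at 20,000 women and 0.154 points at 25,000.

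| Δ | Power at 20,000 | Power at 25,000 |
|---|---|---|
| 0.45 | 74.5% (Table 1: 75%) | 83.3% (83%) |
| 0.50 | 82.9% (83%) | 90.2% (90%) |

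Table 1 reproduces.

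**2. Which observed differences get opposite verdicts.** The upper limit is d + 1.96 × √[(p₁(1 − p₁) + p₂(1 − p₂)) / 12,500], with p₁ = 1.5% and p₂ = p₁ + d. The SE grows with d, so the 0.154 that applies at equal rates must not be reused here.
- d = 0.14 points: SE 0.157, upper limit 0.448, just inside both margins.
- d = 0.19 points: SE 0.158, upper limit 0.5006, just outside both.

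The verdicts therefore conflict for d of about 0.14 to 0.19 points. In counts, 188 events against 209 gives a difference of 0.168 points with 95% CI −0.142 to 0.478, which is non-inferior at 0.50 and inconclusive at 0.45. With 188 events in the full arm, every simplified-arm count from 206 to 211 falls in the gap.

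**3. How often this happens at 25,000 women.** The probability is the difference between the two chances of claiming non-inferiority, using the SE that belongs to each true difference.

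| True difference (points) | SE (points) | P(claim), Δ = 0.45 | P(claim), Δ = 0.50 | Gap |
|---|---|---|---|---|
| 0 | 0.154 | 83.3% | 90.2% | 6.9% |
| 0.10 | 0.156 | 61.0% | 72.6% | 11.5% |
| 0.20 | 0.159 | 35.0% | 47.2% | 12.2% |

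**4. False claims if 0.45 is the intended margin.** At a true excess of 0.45 points the rates are 1.5% and 1.95%, and SE = √[(0.015 × 0.985 + 0.0195 × 0.9805) / 12,500] = 0.165 points. Judged by 0.45, the claim rate is 2.5%. Judged by 0.50, it is Φ(0.05/0.165 − 1.96) = 4.9%.

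**5. Share of the benefit retained.** Retention = 1 − Δ / (expectant risk − 1.5).

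| Expectant risk | Δ = 0.45 | Δ = 0.50 |
|---|---|---|
| 3.0% | 70% | 67% |
| 3.5% | 77.5% | 75% |
| 4.0% | 82% | 80% |

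Within the stated range only 0.45 keeps at least 70%, the lowest share in Table 1, at every expectant rate. Both values reach the 80% criterion only at 4.0%.

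**The case against.** The best defence is that 0.45 already is the working margin, because the sample size sentence is built on it and translates it into a rate below 1.95%. That is a fair reading of the sizing, and it makes 0.45 the natural candidate. But the sentence describes the power of a trial of a given size. It neither names the analysis margin nor overrides the range in the Objective.

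An analysis plan that is not shown may choose a value, and Figure 1, also not shown, may print one. The point is not that detail is absent, though. The formal hypothesis affirmatively states a range where the protocol's own rule needs one number.

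A reader might infer that the investigators mean to choose the margin after seeing the data. The documents do not support that. They twice call the margin pre-stated, and interim results are masked to the investigators. The range leaves such a choice open, but it does not plan one. A reader might also say that a result in the gap is both non-inferior and inconclusive. Whichever Δ is applied, a result gets one verdict, and the fault is that the document does not say which.

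The 4.9% needs the same care. It is an inflation only relative to 0.45. If Δ were declared as 0.50, the error at that boundary would be 2.5%.

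Finally, the case for 0.45 is not one-sided. The text favours 80% retention, and the only 80% row of Table 1 gives 0.50. That row assumes a 4.0% expectant rate, at which 0.45 retains 82%, so 0.50 meets the criterion no more widely. The rationale also says that the choice of margin needs stakeholder consensus, so 0.45 should be proposed with reasons and not presented as the only admissible value.

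**Conclusion.** The point stands as an ambiguity in the primary decision threshold. The gap of 0.05 points is about a third of the standard error. It leaves the verdict undefined in about 7% of trials at a true difference of 0 and about 12% at 0.1 to 0.2 points. These figures assume 12,500 women per arm, a 1.5% full-package risk and the normal approximation with unpooled variance.

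It is not a sample size error. Table 1 is arithmetically sound, and 25,000 women give more than 80% power under either value. It should nonetheless be corrected before outcome data are seen, because the trial's main conclusion rests on this number.

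**What to change.** Before outcome data are seen, state one Δ on the risk difference and print the same number in the Objective, the sample size section and the interpretation scheme. The natural value is 0.45 percentage points, which the sizing sentence already uses and which alone in the range keeps at least 70% at all three expectant rates. Label the 0.50 rows of Table 1 as scenarios only.

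Reconcile the chosen value with the 80% retention criterion. Either say why a lower share is acceptable at expectant rates of 3.0 and 3.5%, or revise the criterion as stated.

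The change is one of wording. The quoted power becomes 83% at 25,000 women and 75% at 20,000. No woman is added to the 25,000 target, but 22,908 becomes the minimum for 80% power, so the lower part of the expected recruitment range would no longer be enough.
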